### Recruitment {20}

Objective 1: Eligible patients will be identified from all new patients referred for KS treatment at each site. Recruitment will occur during waiting times to minimize disruption to patient flow. At the screening visit, staff will obtain written informed consent including discussion of the voluntary nature of research, the specific goals of the study, study procedures, and the potential risks and benefits of study participation.

Objective 2: At each site, providers involved in KS treatment will be requested to participate. They will be recruited by cadre to ensure representation of all providers and administrative roles for quantitative and qualitative evaluations. Eligible patients attending clinic visits will be sequentially sampled to participate in both the clinical evaluation and time-and-motion studies.

### Assignment of interventions: Not applicable.

Sequence generation: {21a} Not applicable. This is a non-randomized observational study.

Sequence generation: {21b} Not applicable.

Allocation concealment mechanism {22} Not applicable.

Implementation {23} Not applicable.

### Assignment of interventions: blinding

Who will be blinded {24a} Not applicable.

How will blinding be achieved {24b} Not applicable.

Procedure for unblinding if needed {24c} Not applicable.

### Data collection and management

Plans for assessment and collection of outcomes {25a}

#### Objective 1 measurements

For each participant we will collect demographic and clinical data regarding KS diagnosis and extent of disease. Thereafter, two clinicians will each measure three lesions using both the manual ruler-based method (standard of care) and SS3D. Standard of care measurement: Participants will have three discrete skin lesions measured, with lesion area determined by ACTG criteria utilizing the product of longest perpendicular diameters. Participants will also have five 3D snapshots of each of the three target lesions taken, measuring lesion area automatically using SS3D AI.

#### Objective 2 measurements

Measurements for Objective 2 will happen in two phases. In phase 1, providers will first measure KS lesions using the manual ruler-based method as per usual standard of care for the first three months. During this time, providers will be trained on use of the adapted SS3D device and protocols. Thereafter, we will administered survey questionnaires to gather information on usability, acceptability, appropriateness, and feasibility of the SS3D intervention. We will also conduct direct observation for workflow mapping, time-and-motion studies, and micro-costing within implementing clinics. Using the System Usability Scale (SUS)^11^, a reliable, well-validated ten-item scale for measuring usability of hardware, software, and applications, we will collect information from providers on multiple aspects of system usability, including need for support, training, complexity. Data regarding acceptability, appropriateness, and feasibility of integrating the device into routine workflows will be collected using the following validated instruments: the Acceptability of Intervention Measure (AIM), Intervention Appropriateness Measure (IAM), and Feasibility of Intervention Measure (FIM)^12^. We will collect data on clinic workflows including any task-shifting, and time associated with clinic visits for patients and providers through time-and-motion studies. Implementation costs will be documented using activity-based micro-costing techniques ^13^.

We will select a random sample of providers to undergo semi-structured interviews to enrich findings from the quantitative measures above.

### Plans to promote participant retention and complete follow-up {25b}

Participants are patients receiving ongoing KS treatment at the study sites and are seen as part of routine clinical care. Retention is promoted through alignment of study activities with routine clinic visits. Patients who discontinue KS treatment or transfer care will have the reason documented.

### Data management {26}

All structured quantitative data will be stored in a centralized, web-based data management scheme using REDCap.^14^ Password-protected access will be strictly limited to study investigators and personnel. For the qualitative data, all audio recordings, transcripts, and results from coding will be stored in password-protected computers. Qualitative data will be recorded as audio files, transcribed, and coded using Dedoose.^15^

### Confidentiality {33}

All raw and analysis data will be stored within a secure computing environment. All potential identifiers will be removed prior to data analysis. Participants will be assigned a unique study identification number at enrollment. All data will be recorded and stored using this identifier rather than personal information. No participant-identifying information will be disclosed in any report or publication arising from the study. SS3D images of skin lesions are stored with the study identification number only. Physical documents containing identifying information are stored in locked cabinets at each site with access restricted to the site principal investigator and designated study staff. Electronic data are protected by encryption and role-based access controls.

### Statistical methods

Statistical methods for primary and secondary outcomes {27a}

#### Objective 1

We will plot a graph for each measurement method. Each graph’s x-axis will represent measurements from clinician 1 and y-axis will represent measurements from clinician 2. For each graph, we will calculate the concordance correlation coefficient (CCC) and coefficient of determination (R-squared). The CCC measures reproducibility (agreement) between clinicians for each method. The method with the higher CCC will be considered the more reproducible, and the method with R-squared closer to 1 will be considered the more accurate. We will also visualize agreement between methods graphically using Bland-Altman plots, and report the mean difference and 95% limits of agreement. To provide a more robust assessment, we will also report mean absolute error and root mean square error to capture the magnitude of differences between methods.

#### Objective 2

System Usability Scale (SUS) scores will be computed following standard scoring procedures (score contributions from items summed and multiplied by 2.5, yielding a score range of 0 to 100). Device usability will further be normalized to generate percentile ranks and graded as either acceptable (score above 68), marginal, or not acceptable. AIM, IAM, and FIM scores will be presented as means, standard deviations, and ranges. Qualitative data collected from semi-structured interviews will be transcribed, coded, and thematically analyzed to identify sub-themes and themes related to SkinScan3D implementation in routine clinical settings. Data triangulation will be applied to cross-validate findings from interviews and direct observation to ensure rigor and validity of the qualitative analysis.

For the cost analysis, we will summarize data to estimate the total program cost of SS3D per patient and per visit, excluding research costs. Costs will be broken down by the categories in Table 2 to identify key cost drivers.

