**Discussion::**

PRIME-KS will provide the first rigorous evaluation of a 3D imaging device for monitoring KS treatment response in routine clinical settings. If SS3D demonstrates superior reproducibility and clinical utility, it could reduce unnecessary chemotherapy exposure and associated toxicities by enabling earlier, more objective assessment of treatment response.

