### Explanation for the choice of comparator {9b}

The comparator is the current standard of care for KS lesion measurement: manual ruler-based assessment using ACTG criteria, which calculates lesion area as the product of the longest perpendicular diameters (Figure 1).^1, 2^ This method was selected because it is the globally recognized standard for KS treatment response assessment used in clinical trials. Comparing SS3D against this established method will determine whether SS3D offers superior reproducibility and accuracy for clinical decision-making.

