### Outcomes {16}

#### Objective 1 (Reproducibility and Accuracy)

##### Primary outcomes:

(1) Concordance correlation coefficient (CCC) for inter-rater reproducibility of KS lesion area measurement. The CCC will be calculated separately for SS3D and for the ruler-based method, based on measurements by two independent clinicians of the same three lesions per participant. The measurement variable is projected lesion area (mm^2^). The method with the higher CCC will be considered the more reproducible. (2) Coefficient of determination (R-squared) for each measurement method, assessing the proportion of variation attributable to true lesion size versus random measurement error.

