If SS3D demonstrates superior reproducibility, accuracy, and clinical utility, it could transform KS treatment monitoring by enabling earlier detection of treatment response, informing timely discontinuation or switch of chemotherapy, decreasing the burden on providers in busy clinics, and introducing a standardized measurement method in KS clinical trials and routine care settings.

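### Objective 1 lets two unranked primaries from one inter-clinician graph each name a winning method, so the plan can call the method with the worse agreement the more accurate one

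*Protocol article*

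**What the plan says.** The Objective 1 primary outcomes in section {16} are two numbered items of equal standing: "1) Concordance correlation coefficient (CCC) for inter-rater reproducibility of KS lesion area measurement" and "2) Coefficient of determination (R-squared) for each measurement method, assessing the proportion of variation attributable to true lesion size versus random measurement error". The Abstract lists the same pair.

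Statistical methods {27a} draws one graph per measurement method, with clinician 1 on the x-axis and clinician 2 on the y-axis. It then states: "For each graph, we will calculate the concordance correlation coefficient (CCC) and coefficient of determination (R-squared"). The decision rule follows: "The method with the higher CCC will be considered the more reproducible, and the method with R-squared closer to 1 will be considered the more" (last word: accurate). Nothing ranks the two outcomes, requires both, or says what to report if they name different methods.

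Section {5} says the statistical analysis plan is integrated in {27a} to {27d}, so this rule is not deferred to another document.

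Three sentences describe what the comparison is for:

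- Section {9b} says it "will determine whether SS3D offers superior reproducibility and accuracy for clinical decision-making".
- The Abstract's Discussion says "If SS3D demonstrates superior reproducibility and clinical utility, it could reduce unnecessary chemotherapy exposure".
- The main Discussion says "If SS3D demonstrates superior reproducibility, accuracy, and clinical utility, it could transform KS treatment monitoring".

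**The concern.** Both statistics describe agreement between two clinicians using one method. Neither compares a reading with a true lesion size, and the Discussion accepts that no gold standard exists. They differ in one respect: the CCC falls when one clinician reads systematically larger, or on a stretched scale, and R-squared does not.

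A split is therefore possible whenever the two methods differ in systematic clinician differences. The rule would then attach the word accurate to the method whose clinicians disagree more. The study would report SS3D as more reproducible and the ruler as more accurate, and the second half would be an artefact of the label. With no order fixed in advance, which result to emphasise would be settled after the data are seen.

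**Working it through.** **1. The plan's own figure.** Table 1 gives 95% limits for the CCC at 150 lesions of 0.73 to 0.85 (CCC 0.8) and 0.86 to 0.93 (CCC 0.9). The Fisher z interval is tanh(atanh(CCC) ± 1.96/√(n − 3)). With n = 150 the half-width is 1.96/√147 = 0.162, giving 0.734 to 0.851 and 0.864 to 0.927. All six cells of Table 1 match to two decimals. The study is sized on the CCC alone; no precision is given for R-squared.

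**2. How the two statistics relate.** For clinician means m1, m2, standard deviations s1, s2 and correlation r:

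- CCC = 2·r·s1·s2 / (s1² + s2² + (m1 − m2)²) = r × bias-correction factor
- R-squared = r²

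The bias-correction factor is 1 only when means and standard deviations are equal. In that case the two statistics order the methods identically, apart from sampling chance. Sample size {19} assumes equal means and variances, but only for SS3D; nothing similar is said of the ruler.

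**3. A worked split (assumed values; shift in SDs of the readings, s1 = s2 = 1).**

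| Method | r | Clinician shift | CCC | R-squared |
|---|---|---|---|---|
| Ruler | 0.95 | 0.4 SD | 2(0.95)/(2 + 0.16) = 0.880 | 0.9025 |
| SS3D | 0.90 | 0 | 0.900 | 0.810 |

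SS3D is labelled more reproducible and the ruler more accurate. With r = 0.95, the ruler's CCC drops below 0.90 once the shift exceeds √(2(0.95)/0.90 − 2) = 0.33 SD.

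**4. How often a split would occur.** Simulation of 50 participants × 3 lesions, 4,000 runs per case. All parameters are assumptions: true-area SD 1, within-person lesion correlation 0.4, offsets in true-area SDs, SS3D without offset unless stated. Reliability is that of a single reading.

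| SS3D / ruler reliability | Ruler offset | SS3D wins CCC | SS3D wins both | Split |
|---|---|---|---|---|
| 0.90 / 0.90 | 0 | about 50% | about 48% | 3% |
| 0.90 / 0.90 | 0.1 | 60% | 50% | 11% |
| 0.90 / 0.90 | 0.2 in both methods | about 50% | 42% | about 15% |
| 0.90 / 0.90 | 0.3 | 97% | 50% | 47 to 49% |
| 0.90 / 0.92 | 0.3 | about 84% | about 9% | about 75% |
| 0.92 / 0.90 | 0.3 | 100% | 91% | 9% |
| 0.90 / 0.85 | 0.3 | 100% | 99% | 1% |
| 0.95 / 0.90 | 0.3 | 100% | 100% | 0% |

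Where only the ruler has a 0.3 SD offset, every split has SS3D winning on CCC and losing on R-squared.

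**5. Sensitivity to clinician pairs.** The table applies one constant offset to all 50 participants. If instead four clinician pairs have 0.3 SD ruler offsets of random sign, the offset partly acts as noise and lowers r as well. The split rate falls to 8 to 9% at 0.90/0.90 and to 19% at 0.90/0.92.

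**The case against.** The strongest reply is that no verdict exists to be contradicted. Section {10} sets a two-part objective, reproducibility and accuracy, and {27a} labels each part separately. More reproducible but less accurate would be a reportable answer to a two-part question. The study calls itself exploratory and plans no formal superiority test, so there is no alpha to breach.

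A reader might go further and infer that the same data could both establish and refute SS3D superiority, because the Abstract's Discussion omits accuracy while {9b} and the main Discussion include it. The documents do not support that. Section {9b} states an aim, answerable one property at a time. The other two sentences are conditional, name different consequences, and also require clinical utility, which Objective 1 cannot supply. None is a decision rule.

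The high split rates can also be challenged. The background speaks of inter-observer variability, which need not be a constant offset, and presents SS3D as the more precise method. Where SS3D is clearly less noisy, the two statistics agree. Several clinician pairs reduce the rate further. {19} also supplements R-squared with Bland-Altman plots, mean absolute error and root mean square error.

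All of this limits the weight of the point. What it does not answer is that the accuracy label rests on a statistic blind to systematic disagreement between clinicians. The supplementary metrics do not repair this, because {27a} still lets R-squared alone name the more accurate method.

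**Conclusion.** The point holds as a labelling and interpretation fault. Two unranked primaries from one graph each name a winner, and one of them can give the accuracy label to the method with the worse agreement. It should be corrected, but it is neither an error-rate breach nor a conflict between formal decision rules.

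Its size is unknown, because the documents give no clinician offset, reliability or number of clinician pairs. Under the assumptions above, the split rate runs from about 0% to about 75%. The upper end is an extreme case: it needs the ruler to be slightly less noisy than SS3D and to carry the same offset throughout. The low rates rest on SS3D being clearly less noisy or on neither method having an offset, and the study has yet to show either.

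**What to change.** Date the change before any Objective 1 analysis.

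- In {16} and {27a}, make the SS3D-minus-ruler difference in inter-clinician CCC for lesion area the deciding contrast for reproducibility. The CCC is the quantity on which {19} and Table 1 size the study.
- Report R-squared beside the bias-correction factor, as the two components of the CCC, and delete the rule that R-squared names the more accurate method.
- Add a sentence on how a split will be described, for example as closer correlation with larger systematic clinician differences.
- Word the claims in {9b}, the Abstract's Discussion and the main Discussion to match, with no accuracy claim resting on inter-clinician R-squared.

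No new data or participants are needed. The costs are real, though. A primary outcome changes after Uganda recruitment began on 1 April 2026, so under {31} an amendment goes to the three ethics bodies and both registry entries are updated. The accuracy half of Objective 1 would also lose its primary outcome. The protocol should say so and rely on the planned between-method measures (Bland-Altman, mean absolute error, root mean square error), described as agreement between methods, since there is no gold standard. If R-squared is kept as a primary, the minimum is to remove its accuracy label and state in advance how a split will be reported.

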**Methods::**

PRIME-KS is a multicountry prospective mixed-methods study with two clinical objectives. Objective 1 is a cross-sectional diagnostic accuracy study comparing SS3D with ruler-based measurement in 50 adults with KS (150 lesions) across sites in Kenya and Uganda. Two clinicians independently measure three lesions per participant using both methods. The primary outcomes are concordance correlation coefficient (CCC) for inter-rater reproducibility, and co-efficient of determination for accuracy. Objective 2 is a non-randomized before-and-after pilot study in 100 patients at three sites, evaluating device usability, acceptability, appropriateness, and feasibility using validated instruments, along with time-and-motion studies and activity-based micro-costing. Prior to these clinical objectives, a formative study used focus group discussions, discrete choice experiments, and human-centered design workshops to refine the SS3D device and protocols with end-user input.

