### Sample size {19}

Objective 1: Assuming that the mean and variance of the area of lesions (as determined by the SkinScan3D method) are the same for two clinicians, then the expected width of a 95% confidence interval (CI) for the concordance correlation coefficient for a given number of lesions examined is shown in Table 1. Therefore, with at least 50 participants with 3 lesions each (150 lesions), we will get a precise estimate of the CCC. To address overinterpretation of the concordance, we will complement the R-squared with additional metrics that capture accuracy more directly, including Bland-Altman plots to assess agreement and systematic bias, mean absolute error, and root mean square error. These measures will allow us to evaluate both correlation and the magnitude and direction of differences between methods.

Objective 2: We will roll out the refined SS3D intervention to 100 participants (50 patients at UCI; 25 at JOOTRH; 25 at Homa Bay). All providers will complete quantitative surveys. We anticipate recruiting providers (up to n=10), clinic administrators and key decision makers (up to n=5) who will participate in semi-structured interviews at each clinic. The final sample of semi-structured interviews will be determined by the point at which thematic saturation is achieved.

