## Discussion

PRIME-KS will provide the first rigorous evaluation of a 3D imaging device for monitoring KS treatment response in routine clinical settings. The study addresses a critical gap in KS care: the absence of a simple, objective, and affordable tool for treatment monitoring that can function effectively, including in resource-constrained settings.

This study provides a unique participatory approach to device development from all stakeholders, ensuring that the SS3D device and protocols are contextually appropriate, acceptable, and designed with the input of the people who will use and benefit from the technology. The formative study activities described under Patient and Public Involvement directly shaped the intervention prior to clinical evaluation, providing a blueprint for participatory approaches to medical device design and implementation in low- and middle-income countries.

Several design considerations merit discussion. The paired within-participant design of Objective 1, in which two clinicians independently measure the same lesions using both methods, is a strength that allows direct comparison of reproducibility while controlling for patient-level variation. The before-and-after design of Objective 2 was chosen over a randomized design because the goal is to characterize the implementation profile of SS3D (usability, acceptability, cost) rather than to demonstrate efficacy; a non-randomized design is appropriate for this purpose and is more feasible given the cluster-level nature of the intervention.

Potential limitations include the lack of a true gold standard for KS lesion measurement. We compare SS3D against the current standard of care rather than against a reference standard such as optical coherence tomography, which is impractical in field settings. Another limitation is that the before-and-after design of Objective 2 is subject to temporal confounding; however, our primary interest is in the implementation profile of the device, for which this design is appropriate. There are also potential challenges of users not fully understanding the technology since it is new, which may yield inappropriate responses during initial implementation; the formative co-creation with potential users, structured training protocol, and think-aloud usability testing are designed to mitigate this.

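### Primary outcome (2) of Objective 1 names the method with the higher between-clinician R-squared the more accurate, but with no reference value it cannot see a bias that both clinicians share

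*Protocol article*

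**What the plan says.** The Objective 1 text under Statistical methods {27a} calls for one graph per measurement method, on which the "x-axis will represent measurements from clinician 1 and y-axis will represent measurements from clinician 2". Both the CCC and R-squared are computed from that graph. The higher CCC marks the more reproducible method, and "the method with R-squared closer to 1 will be considered the more accurate".

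Outcomes {16} lists as the second primary outcome: "Coefficient of determination (R-squared) for each measurement method, assessing the proportion of variation attributable to true lesion size versus random measurement error". The abstract labels it "co-efficient of determination for accuracy". The Discussion states: "Potential limitations include the lack of a true gold standard for KS lesion measurement".

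Sample size {19} adds Bland-Altman plots, mean absolute error (MAE) and root mean square error (RMSE) to guard against overinterpretation, and describes them as more direct measures of accuracy. {27a} defines them as comparisons between the two methods, and {16} ranks them as secondary. Section {5} says the statistical analysis plan is integrated in {27a} to {27d}, so this rule is the plan's operative text and not a detail left to another document.

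**The concern.** Accuracy means closeness to the true lesion area. A statistic built only from two clinicians' readings by the same method shows how well one reading predicts the other; it has no contact with the true area. The gap matters most for SS3D, where the area is computed automatically. If the algorithm misreads lesions in a systematic way, both clinicians inherit the same error.

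Accuracy is half of Objective 1. The rule returns a named winner whatever the data, and the closing paragraph of the Discussion builds on that verdict when it looks ahead to the device's role in treatment monitoring. The fault is symmetric: the ruler could equally be declared the more accurate while biased.

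**Working it through.** **The plan's own figure.** Table 1 is the only precision figure for Objective 1, and it concerns the CCC. With lesions treated as independent, the limits are tanh(atanh(CCC) ± 1.96/√(n − 2)). For n = 150, 1.96/√148 = 0.161. CCC 0.8 gives 0.73 to 0.85 and CCC 0.9 gives 0.86 to 0.93, as printed. Table 1 is not in dispute and does not bear on the accuracy rule.

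**Step 1: what R-squared and the CCC can see.** Let t be the true area, and let the readings be x = a + b(t + e₁) and y = a + b(t + e₂), with the same a and b for both clinicians.
- R-squared = corr(x, y)². It does not change under any linear rescaling of x or y, so a and b drop out.
- CCC = 2·cov(x, y) / [var(x) + var(y) + (mean x − mean y)²]. A shared a cancels in the mean difference, and a shared b multiplies numerator and denominator by b². The CCC is unchanged too.

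Neither primary outcome can therefore detect a shared offset or scale error.

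**Step 2: how the rule can pick the wrong method.** The documents give no lesion-size or error distribution, so these inputs are assumptions: log-normal true area with median 150 mm² and log-SD 0.7 (mean 191 mm², SD 152 mm²), and independent normal error for each clinician, expressed as a fraction s of that SD. With readings b·t + e, R-squared = [b²/(b² + s²)]². RMSE is for the mean of the two clinicians' readings against truth.

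| Method | b | s | R-squared | RMSE against truth |
|---|---|---|---|---|
| Unbiased, noisier | 1.0 | 0.3 | (1/1.09)² = 0.84 | 32 mm² |
| Reads 40% low | 0.6 | 0.1 | (0.36/0.37)² = 0.95 | 98 mm² |
| Reads 50% high | 1.5 | 0.1 | (2.25/2.26)² = 0.99 | 123 mm² |

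In 5,000 simulated trials of 150 lesions, the rule named the 40%-low method more accurate than the unbiased one every time. That frequency and the RMSE values depend on the assumed inputs. The invariance in step 1 does not.

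**Step 3: the stated meaning of R-squared.** {16} describes it as "assessing the proportion of variation attributable to true lesion size versus random measurement error". For x = t + e₁ and y = t + e₂ with independent errors of equal variance, corr(x, y) = var(t) / [var(t) + var(e)]. That correlation is already the share due to true size, and R-squared is its square: a share of 0.80 gives 0.64 and a share of 0.90 gives 0.81.

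**Step 4: what R-squared adds to the CCC.** The CCC equals r times a bias-correction factor. If the clinicians have equal means and variances, that factor is 1, CCC = r, and R-squared = CCC². At Table 1's planning values of 0.8 and 0.9, R-squared would be 0.64 and 0.81, with nothing added. If the clinicians differ systematically, the CCC falls and R-squared does not register it. Under the size assumptions above, with clinician 1 unbiased, clinician 2 reading 2t + 100 mm² and s = 0.1 for both, R-squared is 0.99 and the CCC 0.46.

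**Step 5: the added metrics.** Bland-Altman, MAE and RMSE in {27a} set SS3D against the ruler. A gap shows that the methods disagree, not which one is wrong. The ruler cannot stand in for truth: it takes d₁ × d₂ as the area, whereas an ellipse has area πd₁d₂/4, so the product overstates an ellipse by 4/π = 1.27, or 27%. A projected-area device that is exactly right would still differ from it.

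**The case against.** The study calls itself exploratory, does not alter care, discloses the missing reference standard, and adds agreement metrics precisely because R-squared might be overread. {16} also describes R-squared in terms of reliability more than of truth. These points limit the harm. They leave the rule in {27a} in place, and that rule still produces an accuracy verdict from data that cannot support one.

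Four stronger readings are tempting, and the documents do not support them.
- *A reader might infer that the two primary outcomes must always rank the methods alike, so that one result is counted as two wins.* That needs equal clinician means and variances for both methods. {19} makes the assumption for sizing only, and only for SS3D: "Assuming that the mean and variance of the area of lesions (as determined by the SkinScan3D method) are the same for two clinicians". The Introduction expects inter-observer variation with the ruler, so the rankings can differ.
- *A reader might infer that differences between the clinicians go unnoticed.* The CCC, the other primary outcome, detects them. With clinician 2 reading 1.3 times clinician 1 plus 20 mm², and 5% noise, R-squared ran from 0.85 to 0.99 across assumed log-normal sizes (median 50 to 400 mm², log-SD 0.2 to 1.0). The CCC ran from 0.18 to 0.94 and was the lower of the two in every case. Only shared bias escapes both.
- *A reader might infer that a wrong error share will be reported.* The plan nowhere says that it will report one minus R-squared. Squaring also preserves order, so the misreading in step 3 does not by itself change which method ranks higher.
- *A reader might infer that SS3D is biased.* Nothing in the protocol shows this; the point is that the analysis could not tell.

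**Conclusion.** The concern holds for shared bias and for the accuracy label. The primary rule in {27a} cannot establish accuracy for either method, and it can favour a systematically wrong method over an unbiased one. The insensitivity of R-squared and the CCC to a shared linear bias is exact. The sizes shown (R-squared 0.95 against 0.84, RMSE 98 against 32 mm²) illustrate it under assumed lesion sizes and errors. The relation between R-squared and the true-size share assumes two readings with independent errors of equal variance. The equality of R-squared and CCC squared assumes equal clinician means and variances. The between-method metrics do not repair the rule. It should be corrected before any analysis.

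**What to change.** - In {27a}, delete the rule that R-squared closer to 1 means more accurate.
- In the abstract and {16}, relabel R-squared as between-clinician linear association (precision), and correct its interpretation: under equal error variances the true-size share is the correlation, not its square.
- For each method, report the CCC split into its precision component (r) and its bias-correction component, with the between-clinician mean difference.
- In {19} and {27a}, relabel Bland-Altman, MAE and RMSE as agreement between methods.
- Wherever accuracy is claimed or promised (abstract Background and Methods, {9b}, {10}, {12}, and the closing paragraph of the Discussion), state that it cannot be concluded without a reference standard.

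Replacing R-squared with an intraclass correlation would not help. The absolute-agreement form came within 0.007 of the CCC in simulated sets of 150 lesions with biased raters, and it is equally blind to shared bias.

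No new data are needed, but the accuracy claim is given up. Uganda has been recruiting since 1 April 2026, so changing a primary outcome means an amendment to the ethics committees named in {31} and an update of both registry entries. Kenya has not begun recruiting, and completion of recruitment is expected by Q4 2027, so there is time to do this before analysis.
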